**target area III: improvement of health related physical fitness**	

III.a	Improvement of muscle strength and endurance of back and trunk muscles to prevent states of deconditioning dependent on on inactivity
III.b	Improvement of motor coordination of back and trunk muscles to increase spine stabilization
III.c	Improvement of whole body physical fitness (endurance, flexibility) in sense of enhancement of general physical health resources
III.d	Introduction to several types of physical activity
III.e	Development of a personal network for maintaining physical activity e.g. in fitness facilities

• resource-related mediation of knowledge,

• behavioural modulation and

• physical exercise

We determined the duration of RÜCKGEWINN at 6 months, taking into account the time necessary for the process of behavioural change. In order to have an equal number of sessions compared to IRENA, one session is scheduled weekly for 26 weeks. RÜCKGEWINN will actually be provided in two phases, with the first carried out in 10 consecutive sessions in closed groups. We chose the closed group form, because it is more appropriate to appeal on relevant factors of behavioral change, especially in terms of coping strategies and physical activity enhancement. For anticipated organizational reasons, the second phase of 16 sessions is planned as open access group with partly repeating contents, with the goal set at the participants' empowerment to regular self-determined health enhancing physical activity.

We developed a RÜCKGEWINN manual for therapists and provided some media like for example little ring binders with information cards for participants that will be handed out consecutively each session. We trained several therapists from cooperating certified aftercare facilities to our curriculum. Every patient of this study arm will be allocated to one of those facilities as close as possible to their residence respectively subject to their choice.

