## Methods/Design

### Study Design

The study is designed as multicenter prospective randomised controlled trial in a three-factorial, split-plot plan (3x3xn) characterized as profile analysis (Figure 1) [38]. Thereby "aftercare treatment" appears as whole-plot factor with three categories respectively study arms (booklet, IRENA, RÜCKGEWINN) crossed with the sub-plot time factor that has also three categories (before and after rehabilitation and 12 month follow-up) [39]. The aftercare treatments will be carried out between 2^nd ^and 3^rd ^measurement. The third factor is the nested patient factor and is treated as random [40]. In addition, we stratify and control the trial for the covariables "chronicity staging", "gender", "rehabilitation facility" and "aftercare facility". Therefore, these covariables appear as additional factors.

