### Sample Size and Power Calculation

The sample size calculation was approximated with a 3x3-factorial ANOVA-approach based on the primary outcome and was done with the software "gpower 3.1" [63,64]. To prove an intervention effect with about medium effect size of Cohen's f = 0.27 with an error probability α = 0.05 and power β = 0.8, n ≈ 68 people in each study arm are required for analysis [65]. This was calculated in view of the chosen factorial design with m = 8 estimated fixed parameters. With a supposed drop-out rate of 40% within the progress of the interventions, we need 114 participants in every study arm to begin the assigned aftercare intervention. In addition, we assume that 75% of all participants that were recruited from inpatient or outpatient rehabilitation will start out well with their assigned aftercare treatment. So we need to recruit 152 participants in every study arm or 456 for total sample size (see also Figure 1).

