#### b) IRENA

All participants in this study arm will be introduced into the normal IRENA program (in German: Intensivierte Rehabilitationsnachsorge), which is usual care in Germany [71]. Every patient will be assigned to a certified outpatient aftercare facility near their residential area. Aftercare practitioners and patients can compile an individual therapeutic package from certain appointed therapeutic services [71]. Predominantly resistance training, gymnastics, aquatic exercise, back school and recreation exercises are prescribed by the physicians for aftercare. Most therapies are carried out in open access groups of at least 6 patients without being specific for medical indication. In the IRENA program it is possible to pass the intended 24 exercise sessions with varying frequency per week. Usually, participants complete two or three exercise sessions per week with duration of 90 to 120 minutes per session. Every aftercare facility offers specific therapy combinations at different days a week. Figure 2 shows a weekly therapy plan offered by one of our cooperating facilities.

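### Group delivery in the two active arms is absent from the primary model and the sample size, so the efficacy tests exceed 5% if change is correlated within groups

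*Protocol article*

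**What the plan says.** **Delivery.** Under Aftercare Treatments, section c), RÜCKGEWINN has two phases, "with the first carried out in 10 consecutive sessions in closed groups", followed by 16 sessions in open groups. The closed form was chosen because the authors think it better suited to changing behaviour. For IRENA, section b) says "Most therapies are carried out in open access groups of at least 6 patients"; these groups mix indications, and each patient has an individual package of therapies. In section a), booklet patients receive theirs individually at discharge.

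**Model.** Study Design says "The third factor is the nested patient factor and is treated as random". The equation under Statistical Hypotheses and Analysis agrees: its only random terms are a patient intercept (γ0i) and a patient slope (γ1i). Aftercare facility (AF) and rehabilitation facility (RF) are dummy-coded main effects without a time interaction. There is no term for therapy group. The three primary tests concern β2, β3 and β2 − β3, which are arm differences in slope.

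**Sample size.** "The sample size calculation was approximated with a 3x3-factorial ANOVA-approach based on the primary outcome", with "Cohen's f = 0.27 with an error probability α = 0.05 and power β = 0.8, n ≈ 68 people in each study arm". It is then inflated for 40% drop-out and for 75% starting aftercare. No ICC, group size or design effect appears.

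**The concern.** Patients who go through ten closed sessions together may change together, because of the group, its leadership or its setting. Booklet patients share no such experience, so the design is partially nested: clustered in the active arms and independent in the control arm. A model with patient-level random terms only counts between-group variation in change as independent patient information.

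All three primary comparisons are at stake. If the within-group correlation is positive, their confidence intervals are too narrow and their tests reject too often. The error favours finding a difference between programmes. It is potentially largest for RÜCKGEWINN versus IRENA, because both of those arms can be clustered.

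**Working it through.** **1. The plan's own figure.** Inputs from Sample Size and Power Calculation: f = 0.27, α = 0.05, power 0.8, and "This was calculated in view of the chosen factorial design with m = 8 estimated fixed parameters". Use a noncentral F test with λ = f²N. Reading m = 8 as 7 numerator df plus an intercept (an inference), N = 204 gives power 0.800, which is 68 per arm. Other numerator df do not fit: 2 df needs 136, 4 df needs 169 and 8 df needs 214. The inflation is 68/0.6 = 113.3, rounded up to 114; 114/0.75 = 152; 3 × 152 = 456. The stated figures reproduce under independence, so they contain no allowance for clustering.

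**2. Does the facility adjustment help?** The primary contrast is change from the second to the third assessment. Subtract one from the other within a patient: the AF term has the same value at both times and cancels, while a group effect on aftercare-phase change remains. Several groups may also share a facility, and booklet patients are assigned to no aftercare facility. The AF dummies therefore do not absorb this variation.

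**3. Formulas.** Let m be the number of analysed trial patients per group.
- Design effect in a clustered arm: DE = 1 + (m − 1) × ICC.
- Variance ratio r (true to model) with arms of equal size: r = DE if both arms are clustered equally, and r = (1 + DE)/2 if only one is.
- Actual two-sided type I error at nominal 5%: 2 × [1 − Φ(1.96/√r)].

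**4. Assumed range.** The article gives neither ICC nor m; its only figure is at least 6 patients in IRENA groups, not all of them trial patients. Assume m = 6–10, ICC 0.01–0.10 and equal clustering in both active arms.

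| m | ICC | DE | RÜCKGEWINN vs IRENA | Active vs booklet |
|---|---|---|---|---|
| 6 | 0.01 | 1.05 | 5.6% | 5.3% |
| 6 | 0.05 | 1.25 | 8.0% | 6.5% |
| 8 | 0.05 | 1.35 | 9.2% | 7.1% |
| 10 | 0.05 | 1.45 | 10.4% | 7.7% |
| 10 | 0.10 | 1.90 | 15.5% | 10.4% |

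A simulation (20,000 runs, pooled-variance test of a change score) agrees. At m = 6 and ICC 0.05 it gives 7.8% and 6.5%; at m = 10 and ICC 0.10 it gives 15.2% and 10.3%.

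**5. A milder scenario.** Suppose a closed group of 8 (assumed) loses the planned 40%: 8 × 0.6 = 4.8 analysed. With ICC 0.05, DE = 1 + 3.8 × 0.05 = 1.19. Treat IRENA as unclustered: r = (1 + 1.19)/2 = 1.095, √r = 1.046, and type I error is 6.1%. RÜCKGEWINN versus booklet has the same value.

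**6. Power.** Average the variance inflation over three arms, (1 + 2 × DE)/3, and keep 204 analysed. The 7-df test behind the stated 80% then has power of about 0.72 at DE 1.25, 0.67 at DE 1.45 and 0.56 at DE 1.90. But the global contrast matrix has rank 2, because its third row is the first minus the second. A 2-df test with the same f and N has 94% power under independence, 88% at DE 1.35, 85% at DE 1.50 and 78% at DE 1.90.

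**The case against.** The strongest case on the other side has four parts.

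- **IRENA is not clustered like RÜCKGEWINN.** Its groups are open and mixed in indication, attendance frequency varies, and a patient may attend several. The minimum of 6 counts everyone in the room, so trial patients per group could be close to 1. This stands, and makes equal clustering an upper-side simplification.
- **RÜCKGEWINN clusters may be small.** Group size is not stated, drop-out shrinks the groups, and the last 16 sessions are open. This also stands, and it leads to the 6.1% scenario.
- **The ICC could be negligible.** At ICC 0.01 and 6 per group, type I error is only 5.6% or 5.3%. The harm is conditional on a positive ICC. Even so, the authors chose closed groups for their expected effect on behaviour, which makes an assumption of exactly zero hard to defend.
- **The analysis plan could deal with it.** This does not stand. The article prints the primary model and the sample size inputs, and both omit the group.

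A reader might go further and infer that 68 per arm misses the stated power. The documents do not establish that. The 80% reproduces only for a 7-df test, whereas the rank-2 global contrast keeps about 88% at DE 1.35. Nor does the article give a power for any pairwise test from which a loss could be measured.

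A reader might also assume that attendance lists already identify the group. The Outcomes section records attendance and a disability rating per lesson; it mentions neither group nor therapist.

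**Conclusion.** The concern holds as a conditional fault in the specified primary model. The model has no group-level term for aftercare-phase change although two of three arms receive group treatment, and the facility dummies cannot stand in for one. Any positive ICC of that change makes the standard errors too small, most clearly for the closed RÜCKGEWINN groups.

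The size cannot be fixed from the article. It runs from about half a percentage point of excess type I error or less, through about one point in the milder scenario, to about ten points (RÜCKGEWINN versus IRENA) or five points (versus booklet) at the upper end of the assumed range. The sample size assumes independence and should say so, but a shortfall below 80% for the tests actually planned is not shown.

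**What to change.** 1. **Record** closed-group identity and aftercare facility for every patient as explicit fields, rather than relying on attendance lists.
2. **Model.** Add a partially nested random effect on aftercare-phase change: closed group in RÜCKGEWINN, aftercare facility in IRENA, none for booklet patients. Treat patients who never join a group as singletons, so the intention-to-treat set stays whole. Use Satterthwaite or Kenward-Roger degrees of freedom.
3. **Sample size text.** State that the calculation assumes independent patients. Report power over a range of ICCs and group sizes for the contrasts actually tested: the rank-2 global test and the three pairwise comparisons. The trial need not be enlarged.

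The cost is one recorded field, one or two variance terms and somewhat wider intervals. Facility is only an approximate unit for IRENA, because patients may attend several open groups; the plan should say so.

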### Statistical Hypotheses and Analysis

The primary question refers to the efficacy of the aftercare interventions in comparison to each other. This is related to treatment differences concerning the primary outcome (FFbH-R) during aftercare interventions and quantified by an interaction effect of the corresponding categories of the factors study arm and time between second and third general assessment. Furthermore, the additional single change over time in rehabilitation phases compared to the change effect of aftercare treatment and overall treatment efficacy of rehabilitation plus aftercare intervention should be evaluated for each aftercare treatment. In consideration of adjusting respectively maintaining the multiple α-error for the mentioned aims, multiple hypotheses will be tested in a closed test procedure [72]. Consistent with these objectives and the chosen factorial split-plot design with repeated measures, we use a saturated linear mixed effects model for statistical analysis and stratify for baseline and mentioned covariates [40,73]. To approach the linear change characteristics in two different phases (rehabilitation phases/aftercare treatment) as well as the total change, we use a structured additive linear mixed model with fractional polynomial b-splines with degree l = 1 (linear) and three knots κ_1 _- κ_3_, noted as follows [73]:

I: general form

Y=Uν+Xβ+Zγ+ε

II: reformuled

$$\begin{array}{l} y_{ij}=\beta_{0}+\gamma_{0i}+\beta_{1}t_{ij}+\beta_{2}t_{ij}I_{i}+\beta_{3}t_{ij}R_{i}+\gamma_{1i}t_{ij}+\nu_{1}T+\nu_{2}TI_{i}\\ \;\;+\nu_{3}TR_{i}+\beta_{4}AF_{i}+\beta_{5}RF_{i}+\beta_{6}MPSS_{i}+\beta_{7}G_{i}+\varepsilon_{ij} \end{array}$$

I_i _denotes the indicator variable for IRENA aftercare treatment and R_i _the indicator variable for RÜCKGEWINN aftercare treatment of individual i in a dummy coding with "booklet control" as reference category [73]. The corresponding *β_2 _*and *β_3 _*reflect directly the difference in "slope" of IRENA respectively RÜCKGEWINN to reference "booklet control" and for that reason the efficacy. AF an RF are dummy coded expressions for aftercare respectively rehabilitation facility of patient i, MPSS is also dummy coded variable for chronification stage according to Gerbershagen and G is a dichotomy gender variable. T denotes a suitable construction term for the b-spline for the additional effect (slope) of rehabilitation phases [73].

At first hierarchical, global level in a closed test procedure a likelihood ratio test of the shown specified model against a zero model m_0 _is used with the following global linear hypotheses:

$$H_{0}:C_{AB}\beta =0\;\;H_{1}:C_{AB}\beta \neq 0$$

C is a suitable contrast matrix of fixed interaction effects:

$$C_{AB}=\left(\begin{array}{cccccccc} 0 & 0 & 1 & 0 & 0 & 0 & 0 & 0\\ 0 & 0 & 0 & 1 & 0 & 0 & 0 & 0\\ 0 & 0 & 1 & -1 & 0 & 0 & 0 & 0 \end{array}\right)$$

At second level of the test procedure, three single primary comparisons of change in functional capacity (FFbH-R) during aftercare treatments are performed with *β_i _*~*t(μ,σ^2^)*.:

$$\begin{array}{l} H_{0}:\beta_{2}=0\\ H_{0}:\beta_{3}=0\\ H_{0}:\beta_{2}-\beta_{3}=0 \end{array}\;\;\;\begin{array}{r} H_{1}:\beta_{2}\neq 0\\ H_{1}:\beta_{3}\neq 0\\ H_{1}:\beta_{2}-\beta_{3}\neq 0 \end{array}$$

As shown in the specified model, we consider the stratified analysis to be the primary analysis carried out with the corresponding intention to treat collective. Other analyses are conducted as sensitivity analyses.

To address secondary objectives of the study, the change of secondary outcomes in different aftercare treatments is also assessed. In order to identify effective components or partial goals that should be targeted in aftercare exercise programs, the time varying influence of secondary outcomes on the primary outcomes in the different treatments is modelled by multiple regression modelling.

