**Methods/Design:**

This study aims to examine the efficacy of a specially developed bio-psycho-social chronic back pain specific aftercare intervention (RÜCKGEWINN) in comparison to the current usual aftercare (IRENA) and a control group that is given an educational booklet addressing pain-conditioned functional ability and back pain episodes. Overall rehabilitation effects as well as predictors for compliance to the aftercare programs are analysed. Therefore, a multicenter prospective 3-armed randomised controlled trial is conducted. 456 participants will be consecutively enrolled in inpatient and outpatient rehabilitation and assigned to either one of the three study arms. Outcomes are measured before and after rehabilitation. Aftercare programs are assessed at ten month follow up after dismissal form rehabilitation.

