### Participants

The population we intend to examine are persons with a history of recurrent or enduring back pain episodes due to an unclear or unspecific cause which does not sufficiently explain the extent of experienced pain. Therefore 456 participants will be consecutively enrolled from inpatient and outpatient chronic back pain rehabilitation in six cooperating rehabilitation facilities, which cover the rehabilitative care of Berlin. For inclusion criteria the ICD-10 is used. We included the following diagnoses, in which back pain of unclear or unspecific cause is frequently encoded in medical practice: M51.2 - M51.4, M51.8 - M51.9 (other disk herniation), M53.8 - M53.9 (other specified/unspecified dorsopathies), M54.5, M54.8 - M54.9 (low back pain, other dorsalgia), M54.4 (if radicular symptoms are not dominating). Patients with appropriate diagnosis are asked to take part in the study by the responsible physician. Before baseline assessment, an informed consent is taken to obtain the patients' approval and exclusion criteria are certified. For obvious reasons, we formulated the following exclusion criteria, although patients met the mentioned ICD-10 diagnoses:

• specific reason for back pain, based on a clear cause or diagnosis, which could sufficiently explain its extent (e.g. radicular symptomatic, myelopathesis, inflammatory changes in the spinal column etc.)

• already carried out surgery on the spine within the last year

• additional serious psychic diagnosis

• uncorrected serious visual and acoustic disability

• seriously reduced health status (other diseases) with considerable reduction of dexterity

• application for retirement

• low German language skills (to fulfill the questionnaires)

• age less than 18 or over 65

• residential area outside of Berlin

Eligible patients are randomised and allocated to either one of the three aftercare treatments. To support the participant's recruitment process, a flow chart and a guiding paper was generated and provided to the clinic practitioners and staff.

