### Aftercare Treatments

In the accomplishment of the medical rehabilitation, there will be no deviation from the usual routine treatment, except the described recruitment process. For long term sustainability and the enhancement of the intensity of the rehabilitation process, the investigational aftercare intervention "RÜCKGEWINN" shows formal and didactic divergences from the standard program "IRENA". Due to the fact that also "IRENA" has not been evaluated yet, we included another comparison treatment that has been shown efficacious already [68-70]. All aftercare treatments are shortly described below:

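### The added aim of judging the combined efficacy of rehabilitation and aftercare in each arm has no comparator in this design; the per-arm changes can only be descriptive

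*Protocol article*

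**What the plan says.** The section Statistical Hypotheses and Analysis opens with a comparative question: "The primary question refers to the efficacy of the aftercare interventions in comparison to each other". It then adds further aims. One is to set the change during the rehabilitation phase against the change during aftercare. Another is that "overall treatment efficacy of rehabilitation plus aftercare intervention should be evaluated for each aftercare treatment". The next sentence places these aims under a closed test procedure to control the multiple type I error. The spline model is then introduced with the words "To approach the linear change characteristics in two different phases (rehabilitation phases/aftercare treatment) as well as the total change". The abstract carries the same intention: "Overall rehabilitation effects as well as predictors for compliance to the aftercare programs are analysed".

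On the design, the Participants section states "Eligible patients are randomised and allocated to either one of the three aftercare treatments". The Aftercare Treatments section says of rehabilitation itself: "In the accomplishment of the medical rehabilitation, there will be no deviation from the usual routine treatment, except the described recruitment process". The Study Design section fixes the timing: "The aftercare treatments will be carried out between 2^nd ^and 3^rd ^measurement".

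**The concern.** A claim of efficacy needs an answer to what would have happened without the treatment. For the aftercare programmes, the randomised arms supply that answer relative to each other. For rehabilitation plus aftercare nothing supplies it, because no participant goes without rehabilitation. An arm's movement from the first to the third measurement would then have to stand in for efficacy. In patients with recurrent or enduring back pain who are measured when they enter care, some improvement may occur whatever is done.

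At stake is the conclusion drawn from this one aim. An uncontrolled change could be reported as efficacy under the heading of a randomised trial. The article's Background says that the general effectiveness of inpatient rehabilitation in Germany has been questioned, so readers are likely to look for such a statement.

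**Working it through.** The article gives no figure for this aim, so there is none to reproduce. The check is whether the stated design can identify the stated quantity.

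**Inputs**
- Source of participants (Participants): "456 participants will be consecutively enrolled from inpatient and outpatient chronic back pain rehabilitation in six cooperating rehabilitation facilities". There is no arm without rehabilitation.
- Rehabilitation is routine care for everyone (Aftercare Treatments).
- Three randomised arms: booklet, IRENA, RÜCKGEWINN (Study Design). They differ only between measurements 2 and 3.
- The booklet arm counts as one of the aftercare treatments and is also the reference category of the model (Statistical Hypotheses and Analysis).

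**Step 1: what each arm's change contains.** Let N be the mean change from measurement 1 to 3 that would occur without any treatment (natural course plus any regression to the mean). Let E_k be the combined effect of rehabilitation and aftercare k. The expected change in arm k is

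D_k = N + E_k, for k = booklet, IRENA, RÜCKGEWINN.

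Randomisation makes N the same in all arms.

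**Step 2: what can be solved.** There are three observed changes and four unknowns (N and three values of E_k). No single E_k can be recovered. The differences can:

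D_k − D_j = E_k − E_j.

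N cancels, and so does whatever rehabilitation contributes equally to all arms. What remains is the relative effect of the aftercare programmes. The same holds for measurement 1 to 2: that change is natural course plus rehabilitation, with no group to separate them.

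**Step 3: the same in the written model.** The time terms shared by all arms are β1 and ν1. The departures of IRENA and RÜCKGEWINN from the booklet arm are β2 and β3 for time, and ν2 and ν3 for the rehabilitation-phase term. The total change in the booklet arm is built from β1 and ν1 alone, so it is purely change over time. The total change in the other two arms contains β1 and ν1 plus their own departures. A per-arm statement about combined efficacy therefore always leans on β1 and ν1, which compare nothing.

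**Step 4: is another reading possible?** If the aim meant a contrast between arms, it could not be met for the booklet arm, which is the reference. It would also not concern rehabilitation, which cancels. The within-arm change is the only quantity that fits the wording.

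**Step 5: size of N.** The document does not allow it to be derived. The Outcomes section gives test-retest reliability only as above 0.75 over about one week. That says nothing about how far patients lie from their usual level on entry, nor about the correlation up to follow-up. Entry is by ICD-10 diagnosis, without a threshold on the FFbH-R or on pain, so regression to the mean is possible but not shown.

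**The case against.** The strongest reply is that the article never states a within-arm or before-after test. Where it says what measures efficacy, it points to β2 and β3, which are differences from the booklet arm. Every hypothesis written out after the model is a contrast between arms. The aim is introduced as an addition, the rehabilitation part is already called change over time, and the details may sit in a fuller plan that is not shown.

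Much of this stands. The within-arm reading is an inference, as Step 4 shows, and should be presented as one. A reader might go further and infer that all three arms, the booklet included, will be declared efficacious from their own change. The article contains no such decision rule, although it does place its stated aims under a test procedure. A reader might also want a false-positive rate for such a test; that would need an entry shift and a long-interval correlation which the document does not give. Nor does the Background's remark that effects shrank against a control group show that this happened to uncontrolled studies in general. It most naturally refers to one programme studied with its own control group.

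The reply does not remove the core. A fuller plan could specify a test, but it could not supply a comparator that the design lacks. A between-arm contrast of total change is available from the model, but it answers a different question.

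**Conclusion.** The concern holds for this additional aim only. The design cannot identify the efficacy of rehabilitation plus aftercare in any arm, and the quantity that fits the article's wording is an uncontrolled change. The conclusion rests on three stated facts (rehabilitation for all, aftercare alone randomised, the booklet arm as reference) and on one inference (that the aim refers to each arm's total change). No numerical bias is claimed: natural course is certainly mixed in, and regression to the mean possibly so.

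It would be wrong to infer that the main result is compromised. The tests of β2, β3 and β2 − β3 compare randomised arms and are untouched by this point, and no sample-size figure changes.

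**What to change.** - Reword the aim: for each arm, report the change from measurement 1 to 2 and from 1 to 3 with confidence intervals, described as change from admission. Do not test these changes or label them as efficacy, and take them out of the set of aims covered by the closed test procedure.
- Keep the word efficacy for the randomised between-arm contrasts.
- If a between-arm contrast of the change from measurement 1 to 3 is also reported, describe it as the relative effect of aftercare. Provided that allocation does not alter the rehabilitation phase, it should in expectation repeat the contrast from measurement 2 to 3, and it says nothing about rehabilitation combined with aftercare.
- Align the abstract's sentence on overall rehabilitation effects with this wording.

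The cost is a change of wording; the estimates come from the model already planned. The real downside is that the trial gives up any stand-alone claim about rehabilitation, or about rehabilitation plus aftercare, which it could not support in any case.
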